### 2.9. Data Collection

The intervention group protocol is as follows: the CUMACA-M programme is based on a web application for long-term breast cancer survivors. Participants (LS-BC) in the IG will receive the personalized digital intervention (CUMACA-M programme). Coinciding with the initial session of acceptance to participate in the project and signing a consent form, after the random assignment to the IG, the web application will be presented. Registration will be performed (with username and password), and instructions for use will be provided. At that time, preintervention and sociodemographic data will be collected, as well as measurements of QOL and self-efficacy in the management of the disease. Medical data will be collected in an electronic questionnaire with the help of the SurveyMonkey^®^ tool. For this, a duration of one hour in a face-to-face session is estimated. Subsequent measurements of QOL and self-efficacy variables will be performed at T1, T2, and T3, from the beginning of the intervention. Through the web application, a message will be sent to participants prompting them to complete the questionnaire. This reminder will be reinforced by email and through a WhatsApp^®^ distribution list (differentiated lists for LS-BC of the IG and CG). Satisfaction data with the web application will be collected only at 9 months (T3).

The control group protocol consists of standard care in the PHC nursing office. Since there are no defined nursing care procedures for long-term cancer survivors in PHC in Spain, the LS-BC in the CG will be limited to a single face-to-face consultation of an estimated duration of 1 h, in which participants will receive an informative brochure on topics related to life after cancer and will take the opportunity to offer brief advice on healthy lifestyle habits regarding the importance of a balanced diet and regular exercise. In this session, information about the study will also be provided and, after acceptance to participate, information about the variables to be collected over time (T0, T1, T2, and T3) will be explained. The sociodemographic and medical data of the LS-BC will be collected in T0, as well as the data for the QOL and self-efficacy variables in the management of the disease. An electronic questionnaire will be designed with the help of the SurveyMonkey^®^ (Momentive, San Mateo, CA, USA, 2022) tool to be completed during the consultation on a tablet. Subsequently, participants will be contacted by email and a WhatsApp^®^ (2.22.20.75, Meta Platforms, Menlo Park, CA, USA, 2022)) distribution list with an invitation to complete a questionnaire that will evaluate their QOL and self-efficacy at T1, T2, and T3. Satisfaction data with the care received (standard nursing care) will be collected at 9 months (T3).

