### 2.7. Description of the CUMACA-M Intervention

The personalized digital intervention will be designed in web and mobile application format to facilitate access at any time and from any place, regardless of the device used (computer, tablet, or smartphone). As it is a personalized intervention with the use of different algorithms using artificial intelligence, participants will receive information adapted to their personal needs. As mentioned above, the contents will be developed from an exhaustive review of recommendations and clinical practice guidelines for the care of LS-BC and on the main needs of LS-BC (Phase I of the MRC). Subsequently, the content of the intervention will be agreed upon by a panel of multiprofessional experts from PHC and specialized care, as well as an LS-BC and a representative of an association supporting women with breast cancer.

These contents will be configured in different modules according to the areas identified as priority needs of the LS-BC (for example, fatigue module, lymphedema module, work activity module, and fear of recurrence module), and the principles of the educational intervention characteristic of PHC consultations will be followed (feedback methods, risk personalization, increased awareness, active learning, persuasive communication, goal setting, and actions) [30].

The main page of the digital intervention programme will show a personal record and a video on how to use the programme. The intervention will begin with a screening questionnaire that will measure several concepts that impact quality of life, such as fatigue, anxiety, fear of recurrence, or return to work. According to the responses, participants will receive personalized advice by means of artificial intelligence algorithms on which modules deserve more attention. The web application itself will integrate the measurement of outcome variables that will allow evaluation of the effectiveness of the intervention. The effective management of the topics identified for the intervention will ultimately improve the quality of life of the LS-BC.

In Phase II (feasibility and piloting), the pilot of the intervention will be carried out through a pre-experimental pretest–post-test design with a single group that will pilot the intervention and test the usability of the application to identify areas for improvement and introduce timely modifications.

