### 2.11. Validity and Reliability/Rigour

This study is part of the Medical Research Council framework for the development and evaluation of randomized controlled trials for complex interventions in health. The invitation to participate in the study will always be made by the same researchers and, once the consent is signed, the random assignment will be made to the CG or the IG. Similarly, the initial session in both groups will be conducted by trained nurses who are knowledgeable about the research protocol.

As informed earlier, the instruments that will be used for data collection (QOL-CS and SEMCD) are validated and translated into Spanish and are the most widely used for the targeted population group.

In the IG, the questionnaires will be integrated into the CUMACA-M programme itself and, in the CG, an online electronic tool will be used for their collection. The research consists of a plan for the management and treatment of participants’ data, in which the method of data collection, its custody, and the restriction of access to authorized research team personnel is indicated. This plan was developed with advice from the Data Protection Officer of the Public University of Navarra.

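### Baseline (T0) quality of life and self-efficacy are collected after allocation and within the arm-specific session, so they are open to bias from knowing the arm, and the consent order in the control session needs reconciling.

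*Protocol article*

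**What the plan says.** **Intervention group.** Section 2.9 of the protocol article describes an initial session in which the woman agrees to take part and signs the consent form. Then, "after the random assignment to the IG, the web application will be presented". Next, "Registration will be performed (with username and password), and instructions for use will be provided". The baseline sentence follows: "At that time, preintervention and sociodemographic data will be collected, as well as measurements of QOL and self-efficacy in the management of the disease". Section 2.11 adds: "In the IG, the questionnaires will be integrated into the CUMACA-M programme itself". Section 2.7 says of the programme: "The intervention will begin with a screening questionnaire that will measure several concepts that impact quality of life", with personalised advice given according to the answers.

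**Control group.** Section 2.9 limits control care to one face-to-face consultation of about an hour, in which "participants will receive an informative brochure on topics related to life after cancer" and brief lifestyle advice is given. The same paragraph continues: "In this session, information about the study will also be provided and, after acceptance to participate", the later measurements are explained. The T0 outcomes are completed on a tablet in the course of that consultation.

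**Consent and allocation.** Section 2.11 gives the order for both arms: "once the consent is signed, the random assignment will be made to the CG or the IG". Section 2.6 provides sealed, opaque, sequentially numbered envelopes.

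**Use of T0.** Section 2.8 labels T0 as preintervention in both arms. Section 2.10 compares the arms on the outcomes in its homogeneity check, then takes T0 to T3 as the levels of time in a MANOVA with group, time and their interaction.

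**The concern.** A baseline protects a randomised comparison because it cannot be affected by allocation. Here the IG woman rates her quality of life and self-efficacy after she has been assigned and while the product under test is being shown to her. The CG woman rates hers inside the visit that is the whole of her control care. Both outcomes are self-reported and neither arm is blinded, so knowing the arm can move the answers.

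Two things are at stake. First, T0 is part of the group-by-time comparison, so a difference at T0 caused by allocation becomes part of the estimated effect. Once enrolment is over, no analysis can separate such a difference from chance imbalance, and the homogeneity check cannot tell them apart either. Section 2.10 requires improvement on both outcomes, so a shift in either one can change the conclusion.

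Second, the control paragraph places study information and acceptance inside a visit described as control care. If a site took that literally, women could decline after their arm was fixed, and refusal could differ by arm.

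**Working it through.** **1. The two sequences side by side (section 2.9)**

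| Step | IG | CG |
|---|---|---|
| Consent | In the initial session, before assignment | Acceptance mentioned inside the control consultation |
| Assignment | Stated, before the app is presented | Not mentioned in this paragraph |
| Arm-specific content | App presented, registration, instructions | Brochure and lifestyle advice |
| T0 outcomes | At that same time, after assignment | During the consultation; order relative to brochure and advice unstated |

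That IG baseline follows allocation is stated. Because section 2.11 puts the IG questionnaires inside the programme, completing T0 there also presupposes access to the programme. For the CG, the text establishes only that T0 falls within the arm-specific visit.

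**2. The plan's own figure.** Section 2.5 gives a difference of 0.75, SD 1.8, type I error 5% and type II error 20%. Sidedness is not stated; taking it as two-sided:

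n = 2 × (1.960 + 0.842)² × 1.8² / 0.75² = 90.4, so 91 per arm.

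This reproduces the stated 91, with power 0.803. Moving T0 ahead of allocation leaves it unchanged.

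**3. How a T0 shift carries through.** Let s be the IG-minus-CG difference at T0 caused by allocation, with follow-up values as they would otherwise be. For a change-from-T0 contrast:

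expected estimate = true effect − s.

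The documents give no value for s. As a share of the planned effect, an assumed range gives 0.1/0.75 = 13%, 0.2/0.75 = 27% and 0.3/0.75 = 40%.

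**4. Illustration.** Assumptions: 91 per arm, SD 1.8 at each visit, analysis by change from T0, and correlation r between T0 and follow-up of 0.5 or 0.7 (not in the documents). SD of change = 1.8 × √(2(1 − r)), which is 1.80 or 1.39. SE = SD of change × √(2/91), which for r = 0.5 is 0.267.

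| s | Power for a true 0.75, r = 0.5 | r = 0.7 | Rejection rate with no true effect, r = 0.5 | r = 0.7 |
|---|---|---|---|---|
| 0 | 0.80 | 0.95 | 0.05 | 0.05 |
| 0.1 | 0.68 | 0.88 | 0.07 | 0.08 |
| 0.2 | 0.54 | 0.76 | 0.12 | 0.16 |
| 0.3 | 0.39 | 0.59 | 0.20 | 0.31 |

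The power columns take s in favour of the IG at T0, which lowers power. The rejection rates are the same for s of either sign, but a shift favouring the CG at T0 would bias the contrast upward, whereas one favouring the IG pushes false rejections mainly against the intervention.

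**5. Direction.** IG enthusiasm raises IG T0 and CG disappointment lowers CG T0. Both make s positive and understate the benefit. Advice given to controls just before they answer could raise CG T0, make s negative and overstate the benefit, but that needs the advice to precede T0, which the text does not say.

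**The case against.** A reader might infer that baseline is contaminated by treatment. The text does not show this. In the IG, no module use or personalised advice is placed before T0; what surrounds T0 is presentation, registration and instructions, and the wording may mean that these happen together. In the CG, the questionnaire may come before the brochure and advice. Section 2.8 calls T0 preintervention in both arms. This part of the objection stands.

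A reader might also infer that controls are allocated before they consent. The control paragraph does not mention randomisation. Section 2.11 states consent then assignment for both arms, and the numbered envelopes fit that. The paragraph can be read as the control version of one initial session, with information and acceptance coming first. So this is loose wording to be reconciled, not evidence that selective refusal will undo the randomisation.

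The size of any shift is assumed. The quality-of-life scale has 41 items and a cited test-retest reliability of 0.89, and nothing in the documents says that it would move by 0.3 points within a session. The illustration uses a simple change contrast, whereas section 2.10 plans a four-visit MANOVA. Two of the three plausible mechanisms work against the intervention. Loss of women between assignment and T0 is unlikely when both fall in a session of about an hour.

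Lastly, step order can be a detail that an article leaves to the full protocol. That does not answer the IG point: the article states an order, and the order it states puts baseline after allocation.

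**Conclusion.** The point holds in a limited form. As written, IG baseline outcomes are taken after random assignment and alongside introduction of the app, and CG baseline outcomes are taken within the control consultation in an unstated order. T0 is therefore open to bias from knowing the arm, and possibly to early exposure to the arm-specific session, and it enters the group-by-time analysis.

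The size and direction are unknown. The 13% to 40% range rests wholly on assumed shifts of 0.1 to 0.3 points. The power and rejection figures rest further on the assumed correlations, a change-from-T0 contrast, and a shift confined to T0. They show how sensitive the analysis would be, not what bias to expect. The mechanisms most easily foreseen would understate the benefit.

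The control paragraph of section 2.9 and the consent rule in section 2.11 fit poorly together and should be reconciled. The sample size of 91 per arm is not affected. Because a post-allocation baseline cannot be repaired later and the remedy is nearly free, the order should be settled before enrolment.

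**What to change.** State one order for both arms in sections 2.6, 2.9 and 2.11, within the existing initial session:

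1. Study information and signed consent.
2. T0 quality of life, self-efficacy and sociodemographic data, on the same electronic questionnaire in both arms.
3. Envelope opened.
4. Arm-specific session: app presentation, registration and instructions, or brochure and advice.

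Reword the control paragraph of section 2.9 so that acceptance clearly precedes allocation, in line with section 2.11.

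The fix has one side effect. IG questionnaires are currently built into the app, so a common tool at T0 followed by in-app measurement at T1 to T3 would change platform between baseline and follow-up in the IG only. Preferably use the same questionnaire tool in both arms at T1 to T3 as well; otherwise acknowledge the change as a small limitation.

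The cost is a reordering of steps already planned for the one-hour session, plus some questionnaire set-up if a common tool is used throughout. No extra visit, staff or participants are needed.

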### 2.10. Data Analysis

The statistical analysis of the data will consist of a descriptive presentation of the parameters analyzed in the CUMACA-M programme. Continuous variables will be described as the mean and standard deviation. Categorical variables will be presented as frequencies and percentages. Subsequently, after assessing the normality of the data, corresponding inferential analyses will be performed. During the first stage, an assessment of the homogeneity of the groups (IG and CG) will be carried out by comparing the outcome variables (QOL and self-efficacy), sociodemographic variables, and clinical variables. For this, Student’s t test will be used for the quantitative variables, the chi-square test for the nominal or dichotomous variables (with the corresponding Fisher’s correction, if necessary), and the Wilcoxon test for variables of an ordinal nature. In a second stage, the differences in the outcome variables between the 2 groups (IG and CG) over time (T0, T1, T2, and T3) will be analyzed using multivariate analysis (MANOVA), in which the “group” factors will be incorporated and “time”, as well as the interaction between the 2. In all cases, the significance level will be set at 0.05. The data will be analyzed with the help of SPSS 24.0 software (IBM, Chicago, IL, USA, 2022)).

The intervention will be considered effective if the two variables evaluated (quality of life and self-efficacy) show results of improvement in the intervention group compared to the control group.

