### 2.5. Sample Size

For the calculation of the sample size, a primary outcome measure, quality of life (QOL), was selected [28]. The QOL measure used for this study goes from 1 (extremely poor) to 10 (excellent). A Cohen’s d of 0.4 (effect size) was established, taking into account a difference in quality of life of 0.75 and a standard deviation of 1.8. This effect size has been established, taking into account previous studies [29], and is expected to occur over time, after the intervention. For its part, the type I error has been set at 5% and the type II error at 20%. According to these parameters, 91 subjects will be needed in the intervention group (IG) and 91 subjects in the control group (CG). Depending on the proportion of losses that may occur, the sample size will be increased, calculating an adjusted sample size. In the event that the pilot study suggests making modifications in the calculation of the sample size due to a re-estimation of the effect size, the appropriate corrections will be made before beginning the study. In this study, sample size estimation was performed using the Granmo Calculator, available online in several languages (https://www.imim.cat/ofertadeserveis/software-public/granmo/) (accessed on 15 May 2022.).

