### 2.6. Randomization and Allocation Concealment

The randomization will be by blocks, and this will be divided by the number of subjects in each block (health center). Six primary health centers will participate, so that, in each block/health center, the sample will be 32 subjects (16 IG and 16 CG). This would be a total of 192 participants, which would cover the calculated sample size of 182 subjects).

A list of random numbers generated by the EpiInfo 7.1 programme will be used to randomly assign participants to groups and to minimize the variation in external factors that can affect the comparison. The randomization method will be masked; therefore, the researchers who perform the randomization will not know to which group each subject will be assigned. To mask the randomization process, sealed and opaque envelopes will be sequentially numbered.

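### Baseline balance is tested with p-values at 0.05, while the outcome analysis uses T0 as a response rather than a covariate and omits the health-centre block

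*Protocol article*

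**What the plan says.** Section 2.10 (Data Analysis) sets out two inferential stages, separate from the descriptive presentation that opens the section.

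- **First stage:** "an assessment of the homogeneity of the groups (IG and CG) will be carried out by comparing the outcome variables (QOL and self-efficacy"), plus sociodemographic and clinical variables. The tools are significance tests: "Student’s t test will be used for the quantitative variables, the chi-square test for the nominal or dichotomous variables", with a Wilcoxon test for ordinal variables. The section adds: "In all cases, the significance level will be set at 0.05". It does not say what follows from a significant or a non-significant result.
- **Second stage:** a MANOVA of the outcomes over T0, T1, T2 and T3. Its stated terms are group, time and their interaction. No covariate is named.

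Section 2.6 states "The randomization will be by blocks", each block being a health centre, with six centres of 16 intervention and 16 control participants. Centre does not appear among the terms of the MANOVA.

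Section 2.9 (Data Collection) has the intervention group's baseline questionnaires completed after random assignment, at the session where the web application is presented.

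**The concern.** A baseline p-value in a randomised trial answers a question of little use. What matters for the treatment comparison is how large an imbalance is and how strongly the variable predicts the outcome. Neither can be read from whether p falls below 0.05. With about a dozen tests, a chance signal on some variable is quite likely and may distract readers. A T0 quality-of-life difference that passes as homogeneous can still shift the estimate.

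The remedy is to use the T0 score as a covariate. The planned model has T0 in it, but as one of four responses. The group-by-time interaction then compares change from T0, which over-corrects for a chance imbalance whenever the T0-to-follow-up correlation is below 1 and is less precise than covariate adjustment. At stake are some power and some protection against an unlucky T0 difference, from data that the trial already collects.

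**Working it through.** **Inputs from the protocol.** Section 2.5: "taking into account a difference in quality of life of 0.75 and a standard deviation of 1.8"; "the type I error has been set at 5% and the type II error at 20"%; "91 subjects will be needed in the intervention group (IG) and 91 subjects in the control group (CG"). Section 2.10: 0.05 for all tests. Section 2.8: the list of baseline variables. **Assumed, not in the documents:** r, the correlation of T0 with follow-up QOL, taken as 0.3, 0.5 and 0.7, and an SD of 1.8 at T0 as well as at follow-up. The test-retest value of 0.89 in section 2.8 is a reliability, not a 3- to 9-month correlation.

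**1. The plan's own figure.** n per arm = 2 × (1.960 + 0.842)² × (1.8/0.75)² = 90.4, so 91. It reproduces exactly with a two-sided 5% test.

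**2. Chance signals at baseline.** Listed variables: 2 outcomes, 5 sociodemographic, 5 clinical, 12 in all. Sex is constant because only women are enrolled, which leaves 11.
- Independent tests: 1 − 0.95¹¹ = 0.431; expected number 11 × 0.05 = 0.55.
- Equally correlated tests (simulation): 40%, 34% and 26% at correlation 0.2, 0.4 and 0.6.
- The figure passes one half only from 14 independent tests (51.2%). Adding the four QOL domains would give 15 tests and 53.7%, but the protocol does not say that domains are tested at baseline.

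**3. A T0 difference that passes as homogeneous.** Standard error of a difference = 1.8 × √(2/91) = 0.267. A T0 difference with p = 0.10 is 1.653 × 0.267 = 0.44 points. If the arms differ by D at T0 by chance, the expected follow-up difference due to it is r × D, so the change contrast is shifted by rD − D = −(1 − r)D, opposite in direction to the imbalance.

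| r | Shift of the change contrast | Share of the 0.75 target |
|---|---|---|
| 0.3 | 0.7 × 0.44 = 0.31 | 41% |
| 0.5 | 0.5 × 0.44 = 0.22 | 29% |
| 0.7 | 0.3 × 0.44 = 0.13 | 18% |

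With T0 as a covariate, and a linear relation, the expected shift is zero.

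**4. Precision, one follow-up time.** The SD of change is 1.8 × √(2(1 − r)); the residual SD with T0 as covariate is 1.8 × √(1 − r²). The ratio of the covariate-adjusted variance to the change variance is (1 + r)/2. Power is by normal approximation, 91 per arm, difference 0.75.

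| r | Power, change from T0 | Power, T0 as covariate | Variance saved |
|---|---|---|---|
| 0.3 | 66.1% | 83.8% | 35% |
| 0.5 | 80.3% | 90.1% | 25% |
| 0.7 | 95.2% | 97.6% | 15% |

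Using the t distribution lowers these slightly (for example 83.4% for the covariate analysis at r = 0.3). As a check on the approximation, the multivariate 3-degree-of-freedom interaction test with a constant 0.75 effect at T1 to T3 and equal correlations has power 67%, 83% and 97%, close to the change-from-T0 column.

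**5. If effectiveness were read from the group main effect.** That term averages over all four times, and no effect is expected at T0: (0 + 3 × 0.75)/4 = 0.5625. The 0.75 effect is diluted to about 0.56.

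**The case against.** Several points on the other side stand.

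- **T0 is not ignored.** A reader might infer that the homogeneity tests replace adjustment for baseline. They do not: they are a separate stage, and the group-by-time interaction already compares change from T0. The right comparator for any loss is therefore the change contrast, not a follow-up-only test, and at r = 0.7 the gain is only about 2 percentage points of power.
- **No decision rule.** A reader might infer that a non-significant test will be taken to make adjustment unnecessary, or that a significant one will trigger extra covariates. Section 2.10 says neither. Without such a rule the baseline tests leave the type I error of the effect test unchanged, and randomisation keeps the comparison unbiased on average. Step 3 concerns an unlucky allocation, not a systematic error.
- **T0 may not be a pure baseline.** Section 2.9 collects it after assignment in the intervention group, and section 2.11 puts that group's questionnaires inside the programme while controls use another electronic tool. A T0 difference could then reflect knowledge of assignment or mode of collection, so it is not certain to be chance alone, and adjusting for it is less clean than usual.
- **Centre could be left to an analysis plan.** This article is condensed and no analysis plan is shown. That weakens the point about centre, which cannot be sized because no between-centre variance is given. Section 2.10 does, however, name the terms of the model, and centre is not one of them.

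**Conclusion.** The point holds in a limited form. The protocol plans significance tests of baseline balance that cannot do the job implied for them, and an outcome model that uses T0 less efficiently than it could and leaves out the randomisation block.

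The chance of at least one false baseline signal is up to about 43% on the listed variables if the tests are independent, and lower if they are correlated. To say that a spurious imbalance will probably appear goes beyond these figures.

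Covariate adjustment does better than the change contrast at each r examined: roughly 18, 10 and 2 percentage points of power at r = 0.3, 0.5 and 0.7. These sizes rest on the assumed r, equal SDs at T0 and follow-up, and a single follow-up time. The dilution to about 0.56 applies only if the group main effect is the term used for the conclusion, which section 2.10 leaves open.

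This is worth changing before the analysis. It does not invalidate the trial.

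**What to change.** In section 2.10:

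1. Replace the first stage with a descriptive baseline table by arm (means and SDs, counts and percentages) without p-values.
2. Prespecify that QOL and self-efficacy at T1, T2 and T3 are compared between arms with adjustment for the T0 value of the same scale and for health centre, however baseline looks. A repeated-measures model with the T0 means constrained to be equal would serve the same purpose for T0.

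In section 2.9, have the T0 questionnaires completed after consent but before the assignment is disclosed, so that T0 is a true pre-randomisation covariate.

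The analysis change costs wording only: T0 scores and centre are already recorded, and fewer tests are run. The collection change reorders steps around the same initial session and adds no measurement.

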### 2.8. Evaluation Measures

The independent variable will be the CUMACA-M programme, since it is expected that, after its application, there will be changes in the values of the dependent variables (see below). Measures of the variables of interest will be collected, both in the IG and in the CG, at the preintervention time (T0), at 3 months after the intervention (T1), at 6 months (T2), and at 9 months (T3).

The dependent variables analyzed will be quality of life (QOL) of cancer survivors (CS) and self-efficacy in the management of cancer sequelae.

Quality of Life—Cancer Survivors (QOL-CS scale, Spanish version): it will be used with cancer survivors in QOL [24] and its 41 items in the 4 domains of QOL (physical, psychological, social, and spiritual well-being) will be measured on a Likert-type scale from 1 (extremely poor) to 10 (excellent). The overall QOL-CS tool test–retest reliability was 0.89, with subscales of physical 0.88, psychological 0.88, social 0.81, and spiritual 0.90 [24]. Cronbach’s alpha coefficient is a measure of agreement between items and subscales. The analysis revealed an overall r = 0.93. Subscale alphas ranged from r = 0.71 for spiritual well-being, r = 0.77 for physical, r = 0.81 for social, and r = 0.89 for psychological. Cronbach’s alpha is 0.93. Subscale alphas ranged from 0.71 for spiritual well-being, 0.77 for physical, 0.81 for social, and 0.89 for psychological [24].

Self-Efficacy for Managing Chronic Disease 6-Item Scale (SEMCD−6, Spanish version): it will be used to assess self-efficacy in the management of cancer sequelae and promotion of healthy lifestyles [31]. It is structured into 6 items related to the control of symptoms, role performance, emotional state, and communication with health professionals. In this study, the Spanish version of the SEMCD will be used that is structured into 4 items compared to the 6 in the English version [31].

The sociodemographic data of the LS-BC (age, sex, marital status, educational level, and employment status) will be collected through an ad hoc questionnaire at the beginning of the intervention. Data on the medical history (type of breast cancer, type of treatments, time elapsed since the end of active cancer treatment, relapses, and comorbidities) and follow-up will be collected through the clinical history of the LS-BC.

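### The trial is sized for one 0.75-point QOL difference, but the planned MANOVA counts baseline as an outcome and names no deciding term or visit

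*Protocol article*

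**What the plan says.** Section 2.5 of the protocol article chooses QOL for the calculation ("a primary outcome measure, quality of life (QOL), was selected") and bases it on "a difference in quality of life of 0.75 and a standard deviation of 1.8", with 5% type I and 20% type II error, giving 91 women per arm. No visit is attached to that difference; it "is expected to occur over time, after the intervention".

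Section 2.10 first compares the arms for homogeneity at baseline. It then states that differences between the arms "over time (T0, T1, T2, and T3) will be analyzed using multivariate analysis (MANOVA"), with group and time as factors "as well as the interaction between the 2". One significance level, 0.05, serves for every test. The intervention counts as effective if both QOL and self-efficacy show improvement over control; no visit, model term or contrast is named.

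On timing, Section 2.8 places the measurements "at 3 months after the intervention (T1), at 6 months (T2), and at 9 months (T3"), while Section 2.9 says of the intervention arm that they "will be performed at T1, T2, and T3, from the beginning of the intervention".

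**The concern.** A sample size is a promise about one particular test. Here that test is a 1-df comparison of two means, whereas the analysis offers a group effect, a time effect and an interaction. Two of these bear on the treatment comparison, and neither is the sized contrast.

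- The group effect is the arm difference averaged over all four occasions, including T0, before the programme has been used.
- The interaction asks whether the arm difference changes at all between occasions. It has 3 df, no direction and no single estimate.

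So the reader of the results could not say which p-value settles the QOL question, and the choice could be made after the data are seen. Listing T0 among the outcomes also forgoes its best use, as a covariate that sharpens the post-baseline comparison.

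**Working it through.** **Inputs.** Difference 0.75, SD 1.8, 91 per arm, two-sided 5% and 80% power (Section 2.5; sidedness is not stated, but two-sided reproduces the figure). Four occasions T0 to T3 (Sections 2.8 and 2.10). Assumed, because the article gives no figure: SD 1.8 at every occasion and an equal correlation ρ between occasions, taken as 0.3, 0.5, 0.7 and 0.8. No losses.

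**1. The plan's own figure.** n per arm = 2 × 1.8² × (1.960 + 0.842)² / 0.75² = 90.4, rounded up to 91. This matches. A one-sided test would give 72, and the rounded standardised effect of 0.4 (0.75/1.8 = 0.417) would give 99. The size is therefore that of a two-sided comparison of two means at one unnamed time, with no use of baseline or repeated measures.

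**2. Group effect over T0 to T3 (1 and 180 df).** The effect is the mean of the four arm differences.
- Constant 0.75 at T1 to T3: (0 + 0.75 + 0.75 + 0.75)/4 = 0.5625.
- Linear growth: (0 + 0.25 + 0.50 + 0.75)/4 = 0.375.

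SE = √[(2/91) × 1.8² × (1 + 3ρ)/4]. At ρ = 0.5 this is 0.211, so the ratios are 0.5625/0.211 = 2.67 and 0.375/0.211 = 1.78.

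**3. Group-by-time interaction (multivariate, 3 and 178 df).** Noncentrality = (91/2) × SS / [1.8² × (1 − ρ)], where SS is the sum of squared deviations of the four arm differences from their mean.
- Constant effect: SS = 0.5625² + 3 × 0.1875² = 0.422. At ρ = 0.5 the noncentrality is 11.8.
- Linear growth: SS = 2 × (0.375² + 0.125²) = 0.3125. At ρ = 0.5 it is 8.8.

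**4. Baseline-adjusted contrast at one visit (1 and 179 df).** SE = √[(2/91) × 1.8² × (1 − ρ²)]. At ρ = 0.5 this is 0.231, and 0.75/0.231 = 3.25.

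**Power at 91 per arm (noncentral F)**

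| Test and true effect | ρ 0.3 | ρ 0.5 | ρ 0.7 | ρ 0.8 |
|---|---|---|---|---|
| Group effect, constant 0.75 | 86% | 76% | 66% | 62% |
| Group effect, growing to 0.75 | 53% | 42% | 36% | 33% |
| Interaction, constant 0.75 | 67% | 83% | 97% | >99% |
| Interaction, growing to 0.75 | 53% | 69% | 90% | 98% |
| Baseline-adjusted, 0.75 at the named visit | 83% | 90% | 97% | >99% |

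For 80% power the adjusted contrast needs 83, 68, 47 and 33 women per arm at these four correlations, which is below the planned 91 in every case.

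**The case against.** The best defence is that in a group-by-time design the interaction is the natural test of a difference in change, and T0 does enter it. That stands. For a constant 0.75 the interaction has 83% power at ρ = 0.5 and more at higher correlations, and at ρ = 0.3 the group effect (86%) slightly exceeds the adjusted single-visit contrast (83%). But the article does not say that the interaction decides. Even if it did, an omnibus 3-df result gives neither the direction nor the size of the difference on which the trial was sized.

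A second defence is that an analysis plan not shown here may supply the detail. That covers finer specification. It does not cover what the article itself fixes: T0 as an outcome value, three terms at a common 0.05, and a success rule that refers to none of them.

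Several stronger readings are tempting, and the documents do not support them.

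- **Type I error of 11 to 12%.** This would be the two-sided rate, per outcome, if significance at any of three visits counted. The plan states no such rule. Counting only benefit, the rate is about 5 to 6% per outcome (ρ 0.5 to 0.7), and the success rule also requires both outcomes to improve.
- **A joint test of both outcomes cannot show that each improved.** Section 2.10 does not say that the outcomes are pooled. Treating the occasions of one outcome as the multivariate response is an equally fair reading, and it is the one used above.
- **The sample is too small, or the 0.75 is not tested at all.** The first is contradicted by the last row of the table. The second ignores what the interaction carries.
- **An effect that fades by 9 months would be a false positive.** It would be a real early effect, and the article does not require benefit to persist.
- **T3 must be the deciding visit.** It is defensible, but Section 2.5 speaks of an effect over time, which would equally suit an average of T1 to T3.

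**Conclusion.** The point holds as a mismatch between the sized contrast and the stated analysis, together with a success rule that names no contrast. With the same 182 women, power for a true 0.75 effect that is constant or builds up runs from 33% to over 99%, depending on which unnamed term decides, on the time course and on the correlation.

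The figures assume SD 1.8 at each occasion, equal correlations of 0.3 to 0.8 and complete data. The dilution of 0.75 to 0.5625 or 0.375 depends on none of these, only on the time course. The mismatch does not always cost power, and it does not call for more participants. The difference in time origin between Sections 2.8 and 2.9 is real but minor.

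**What to change.** 1. In Section 2.10, name one primary between-group QOL contrast before any data are seen: for example T3 at 9 months, or the average of T1 to T3 if that is what an effect over time means.
2. Estimate it from a mixed model or ANCOVA on post-baseline values, with T0 QOL as covariate and health centre (the randomisation block in Section 2.6) as a factor. Report the difference with a 95% confidence interval.
3. Fit a separate model of the same form for self-efficacy. Tie Section 2.5 to the QOL contrast and the success rule to both contrasts; other visits become secondary.
4. Collect T0 in both arms before allocation is disclosed. Section 2.9 takes it after assignment in the intervention arm, which weakens it as a covariate.
5. Align the time origin in Section 2.8 with that in Section 2.9.

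The cost is about a paragraph of wording and a change in the order of the first session. No new measurements and no larger sample are needed. The downside is that one visit or average must be chosen in advance, and an effect confined to other visits then becomes a secondary finding.
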